Fulfil National Institute for Health and Care Excellence [3] clinical criteria for osteoarthritis: • Age > 45 years; • Have activity related joint pain; and • Have morning stiffness ≤30 min. Average knee pain severity ≥4 on 11-point numeric rating scale (NRS, where 0 = no pain, 10 = worst pain possible) in the past week History of knee pain on most days for at least 3 months Aged < 81 years – due to potential safety reasons and additional co-morbidities Body mass index (BMI) ≥ 28 kg/m^2^ and < 41 kg/m^2^. The lower BMI limit was chosen according to recommendations [39] that VLCD are effective in supporting weight loss in people with a BMI > 27. The upper limit was chosen as these individuals often require more extensive intervention and for possible safety reasons Member of Medibank with a level of cover that includes arthroplasty surgery Able to give informed consent and to participate fully in the interventions and assessment procedures Willing to follow advice for self-management, participate in exercise/physical activity and/or participate in a weight loss program if part of their treatment program Have the ability to weigh themselves (e.g. have access to the same set of bathroom scales)	Booked for knee surgery on either knee Have had all eligible knee joints replaced by arthroplasty Knee surgery within the past 6 months Unable to speak or read English Self-reported diagnosis of rheumatoid arthritis or other inflammatory arthritis Other medical condition or upcoming medical procedures that in the opinion of the research staff and/or investigators would preclude participation Private health insurance claims related to cancer treatment or inpatient neurological rehabilitation in the previous 12 months, palliative care, or acquired brain injury Unable to use/access a telephone and internet For those identified as at risk from the pre-exercise and falls screening, doctor does not give clearance Used low-calorie meal replacement products (e.g. Optifast/Optislim) for weight loss in previous 6 months Currently, or in the past 6 months, undertaking regular strengthening exercises for the knee Unable to undertake VLCD for medical reasons including: i. Self-reported diagnosis of Type 1 diabetes ii. Self-reported Type 2 diabetes requiring insulin or other medication apart from metformin iii. Self-reported warfarin use iv. Stroke or cardiac event in previous 6 months v. Unstable heart condition vi. Fluid intake restriction

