### Randomisation allocation concealment and blinding

The randomisation schedule is computer generated and prepared by the study biostatistician. Following completion of the baseline questionnaire, participants are randomly allocated to either the *Exercise* group, the *Exercise plus weight management* group, or the information only (*Control*) group. Due to the differences expected to be observed between treatment groups (effect size of 0.3) and between the least-performing treatment group and the control group (effect size of 0.4), to minimise the number of control group participants required, we will recruit fewer participants in the control group than in either treatment group: see details in the Trial sample size section below. This leads to a randomisation ratio of 5:5:2 (for every 5 participants randomised to a treatment group, we will only randomise 2 to the control group). We expect to see a smaller difference between the two treatment groups than between the least-performing treatment group and the control group. Randomisation will be stratified by history of knee surgery (arthroscopy or contralateral arthroplasty). Participants allocated to the *Exercise* group are randomly allocated to one of three physiotherapists. Participants allocated to the *Exercise plus weight management* group are randomly allocated to one of the same three physiotherapists as in the *Exercise* group, and one of five dietitians. If a physiotherapist or dietitian is unavailable (e.g. sick, on holidays), participants are re-randomised to another available clinician. To conceal group allocation, a researcher not involved in participant recruitment accesses the randomisation schedule via a password-protected computer program.

Given that all primary and secondary outcomes are self-reported, participants are also the assessors. Participants are blinded to study hypotheses, however the components of each treatment arm are disclosed during recruitment. This replicates real-world conditions whereby consumers are fully informed about the nature of the treatment components before choosing whether or not to participate/receive an intervention. Physiotherapists and dietitians are not blinded to group allocation.

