### Outcomes

Outcome measures and time points are described in Table 4. Our primary and secondary outcome measures are recommended and validated for knee OA trials [56, 57] and are measured at baseline, 6 and 12 months.

**Table 4 Tab4:** Summary of measurements to be taken

Domain	Data collection instrument	Time points		
		Baseline	6 M	12 M

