### Secondary outcomes

Secondary outcome measures include:
i)Self-reported weight, measured in kilograms. Participants are asked to use the same set of scales for these measures across the time points;ii)Physical activity, assessed using the Incidental and Planned Exercise Questionnaire (IPEQ-W) [61];iii)Health-related quality of life, measured using the Assessment of Quality of Life Instrument (AQoL-8D) [62];iv)Global rating of change, scored on a 7-point Likert scale for “Overall change in your study knee since you began the study” from “much worse” to “much better” [63];v)Satisfaction with care, scored on a 7-point Likert scale for “Overall satisfaction with the care you received in this study” from “extremely unsatisfied” to “extremely satisfied”;vi)Self-reported appointments with an orthopaedic surgeon;vii)Depression, anxiety, and stress, measures on the Depression, Anxiety, and Stress Scale (DASS-21) [64];viii)Self-reported total knee joint replacement and knee arthroscopy surgery;ix)Willingness to undergo surgery, measured on a 5-point Likert scale ranging from “definitely not willing” to “definitely willing”.

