### Trial sample size

The primary outcomes of this trial include changes in pain (NRS) and physical function (WOMAC) over 6 months and the intervention will be considered beneficial if it changes either one or both of the primary outcomes. A Cochrane Review shows that exercise has a moderate effect size for pain and function in knee OA [10]. Calculations thus assume an effect size between the least-performing treatment group (presumed to be the *Exercise* group) and the control group of 0.4. Given that the effect size between two treatments will be less than between treatment and control, we assumed an effect size of 0.3 between the *Exercise* group and the *Exercise plus weight management* group. We chose 0.3 because any smaller effect is unlikely to be clinically relevant or cost-effective to implement in real-world settings given the considerable expense of the weight management program relative to the exercise components of this combined intervention. Calculations also assume a correlation between baseline and follow-up measurements of 0.4, power 80, 15% loss to follow-up (based on our previous research [71, 72]), and two-sided significance level of 0.05. Based on these calculations we require 173 participants in each treatment group, and 69 participants in the control group arm, giving a total sample size of 415 participants.

There are different levels of clustering for each of the three groups; in the *Exercise* group, participants are clustered by physiotherapist, in the *Exercise plus weight management* group, people are clustered by physiotherapist and dietitian, and in the control group, there is no clustering. Given the geographical and demographic spread of participants, we expect that the intra-cluster correlation of outcomes treated by the same dietitian or physiotherapist to be of the order of 0.01. Modifying the formulae [73] to allow for correlations between baseline and follow-up measurements, and assuming that there are five dietitians delivering the *Exercise plus weight management* treatment, the effect size that can be detected between the *Exercise* and the *Exercise plus weight management* groups with 80% power given the originally calculated sample size increases slightly to 0.32.

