### Analysis

We will use intention-to-treat analyses, using multiple imputation to account for missing data and details on the imputation will be reported [74]. Participants will be included in their randomised treatment groups regardless of their post-randomisation behaviour. *P* values less than 0.05 will be considered significant. Outcomes (primary, secondary, and determinants) will be compared between groups as follows: i) *Exercise* vs *Exercise plus weight management*; ii) *Exercise* vs control, and; iii) *Exercise plus weight management* vs control. For continuous data, mean differences in change over time between these groups will be estimated using linear regression models fit to data from both follow-up time points, with random effects for participants, and accounting for clustering by physiotherapist and dietitian in the *Exercise* and *Exercise plus weight management* groups. Models will be adjusted for the stratification variable (history of knee surgery) and values of the outcome at baseline. Terms for time and treatment will be included, with an interaction between the two. Regression assumptions will be assessed using standard diagnostic plots. For binary outcomes, logistic regression models will be fit using generalised estimating equations to account for clustering, with risk differences and 95% confidence intervals calculated. This will include a comparison of the proportion of participants in each group whose improvement meets or exceeds the minimal clinically important difference for each of the primary outcomes. For ordinal outcomes, proportional odds models will be fit similarly. Multinominal models will be applied if the assumption of proportional odds is not valid. To assess the sensitivity of the results for the primary outcomes in situations in which the outcomes are missing not at random, we will apply a pattern-mixture approach that involves fitting regression models that adjust for departures from the missing at random assumption [75].

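### If knee-surgery rates at 6 and 12 months are roughly 1.5–5%, the stated risk-difference analysis against 69 controls inflates false findings of excess surgery; pre-specify a sparse-event method for this outcome

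*Protocol article*

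**What the plan says.** The Analysis section sets one method for binary outcomes: "logistic regression models will be fit using generalised estimating equations to account for clustering, with risk differences and 95% confidence intervals calculated". Its scope is wide: "Outcomes (primary, secondary, and determinants) will be compared between groups as follows", followed by three pairwise contrasts, two of them against control. Among the secondary outcomes is "Self-reported total knee joint replacement and knee arthroscopy surgery", which Table 4 schedules at 6 and 12 months.

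On arm sizes, Trial sample size says "we require 173 participants in each treatment group, and 69 participants in the control group arm, giving a total sample size of 415 participants", with 15% loss to follow-up allowed for. The small control arm is deliberate: "This leads to a randomisation ratio of 5:5:2".

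Table 1 (eligibility) excludes anyone "Booked for knee surgery on either knee" and anyone with knee surgery in the past 6 months. Both exclusions tend to lower the number of early operations. No expected surgery rate is given. The Analysis section has a fallback for ordinal outcomes when proportional odds fails, but none for a binary outcome with few events.

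**The concern.** A logistic model estimates each arm's risk on the log-odds scale. If no control participant has surgery, that arm's log-odds run off towards minus infinity and its fitted risk goes to zero. The usual delta-method interval for the risk difference then takes almost no variance from the control arm, although 69 people without an event are compatible with a true risk of several per cent. The interval reflects only the intervention arm's uncertainty and is too narrow.

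The error is lopsided. With 173 against 69, the arm likely to have no events is the control arm, so false findings point almost entirely towards more surgery with the intervention. The protocol treats P < 0.05 as significant, so a handful of operations against none could be reported as a significant increase when there is no effect.

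**Working it through.** **Arm sizes.** Inputs from Trial sample size: effects 0.3 and 0.4, correlation 0.4, 80% power, two-sided 0.05, 15% loss.
- Intervention arms: 2 × (1 − 0.4²) × (1.960 + 0.842)² / 0.3² = 146.5, so 147; 147/0.85 gives 173.
- Control arm at ratio 2.5: (1 + 1/2.5) × 0.84 × 7.85 / 0.4² = 57.7, so 58; 58/0.85 gives 69.
- Total 173 + 173 + 69 = 415, as stated. After 15% loss: 0.85 × 69 ≈ 59 and 0.85 × 173 ≈ 147.

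**Assumptions.** The true surgery rate p is the same in every arm and, because the protocol gives none, is varied from 0.5% to 8%. The interval is the unadjusted delta-method (Wald) one: p₁ − p₀ ± 1.96 √[p₁(1 − p₁)/n₁ + p₀(1 − p₀)/n₀].

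**When a zero-event control arm gives a false excess.** With p₀ = 0 the lower limit is above zero when x₁ > 3.84 n₁/(n₁ + 3.84). That is 3.76 for n₁ = 173 and 3.74 for n₁ = 147, so four events are needed in either case.
- 3/173 against 0/69: 1.7% (−0.2% to 3.7%), includes zero.
- 4/173 against 0/69: p₁ = 2.31%, SE = √(0.0231 × 0.9769/173) = 1.14%, so 2.3% (0.1% to 4.6%), excludes zero. For the same data Fisher's exact p = 0.58 and the Miettinen–Nurminen score interval is −3.0% to 5.8%.

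**Error rates.** P(no control events) = (1 − p)^n₀. False-excess and false-reduction rates come from exact enumeration of the two binomials; 2.5% is nominal in each direction.

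| True rate | P(0 of 69) | P(≥4 of 173) | False excess, 69 v 173 | False reduction, 69 v 173 | False excess, 59 v 147 |
|---|---|---|---|---|---|
| 0.5% | 71% | 1.2% | 0.8% | 0.0% | 0.5% |
| 1% | 50% | 9.7% | 4.8% | 0.1% | 3.4% |
| 1.5% | 35% | 26% | 9.2% | 0.3% | 7.4% |
| 2% | 25% | 46% | 11.3% | 0.4% | 10.3% |
| 3% | 12% | 76.5% | 9.8% | 0.7% | 10.9% |
| 4% | 6.0% | 92% | 7.1% | 0.9% | 8.4% |
| 5% | 2.9% | 98% | 6.0% | 1.1% | 6.5% |
| 8% | 0.3% | about 100% | 5.1% | 1.4% | 5.4% |

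Zero-event control arms account for nearly all of the false excess at 2% (11.3 of 11.3 points) and 3% (9.4 of 9.8), and for about half at 5% (2.8 of 6.0). Logistic GEE fits with no control events behaved as described: control log-odds ran to about −25 or lower, and the control arm added almost nothing to the variance of the risk difference.

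**Rough multiple-imputation check.** Assumptions: 15% missing; within-arm imputation with a weak Beta(a, a) prior, a = 0.25 or 0.5; 30 imputations; Rubin's rules; 4,000 trials per rate. False excess was 2.5–4.5% at a 1.5% rate, 5.4–7.5% at 2%, 6.9–8.4% at 3%, 6.9–8.1% at 4% and 5.7–6.3% at 5%. Allowing for other imputation models, about 5–10% at rates of 2–5% is a fair summary.

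**Score method.** A Miettinen–Nurminen test at 69 against 173 has a two-sided error of 3.8–4.9% for rates of 1–8%. It is asymmetric too (false reduction 3.0–4.3%), but stays within 5% overall.

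**The case against.** Four points on the other side have weight.

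- **The rate is unknown.** Nothing in the protocol places the trial in the troublesome band. Excluding people already booked lowers early events, but participants have pain of at least 4 out of 10, hold arthroplasty cover, and arthroscopy counts as well. This stands, and the conclusion has to be conditional.
- **The interval type is not named**, and a rule for sparse cells may sit in an analysis plan that is not shown. This also stands; the delta-method interval is an inference from common practice. The point is nonetheless more than a missing detail: the protocol states one model for all binary outcomes, and that model suits this outcome poorly.
- **Multiple imputation is planned**, and imputed controls restore some variance to that arm. The check above confirms a reduction, most at rates of 2% and below, but not removal.
- **A separated fit is conspicuous**, so an analyst may notice it. That argues for fixing the alternative beforehand, not after seeing the data.

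A reader might infer that a zero-event control arm is likely and that the interval then shows excess surgery. The figures do not support this. Zero events are more likely than not only at rates below about 1% (69 controls), where four or more intervention events are uncommon and the two-sided error is about nominal (4.9% at 1%). A reader might also infer that surgery avoidance is the insurer's declared interest; the protocol does not say so.

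**Conclusion.** The concern holds conditionally. If the true knee-surgery rate at 6 or 12 months is roughly 1.5–5% and the usual delta-method interval is used, false findings of excess surgery against control run at about 6–11% per comparison on complete data, and about 5–10% at rates of 2–5% under a rough imputation model, against 2.5% nominal. At 0.5% there is no inflation, and above 5% it fades towards 5%. The cause is few events in a small arm, not the number of clinicians.

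This affects one secondary outcome. Pain and function, the common binary outcomes and the primary conclusions are untouched. The figures rest on an assumed rate, an assumed interval type and equal true risks in all arms.

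**What to change.** For self-reported knee surgery at 6 and 12 months only, pre-specify one of two methods before the data are seen:
- Firth-penalised logistic regression adjusted for history of knee surgery, fitted within each imputed dataset. This keeps the planned imputation. Its error rate was not computed here.
- A Miettinen–Nurminen score risk difference with 95% CI, stratified by history of knee surgery, on observed data. This keeps the risk-difference scale.

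Keep the logistic-GEE risk difference for common binary outcomes such as the responder proportions.

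The cost is a short addition to the analysis plan. Clinician clustering is not modelled for this outcome, which matters little with so few events. The score interval is not routinely pooled across imputations, so that option departs from the planned imputation and the plan should say so.

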## Abstract

**Background:**

Although education, exercise, and weight loss are recommended for management of knee osteoarthritis, the additional benefits of incorporating weight loss strategies into exercise interventions have not been well investigated. The aim of this study is to compare, in a private health insurance setting, the clinical- and cost-effectiveness of a remotely-delivered, evidence- and theory-informed, behaviour change intervention targeting exercise and self-management (*Exercise* intervention), with the same intervention plus active weight management (*Exercise plus weight management* intervention), and with an information-only control group for people with knee osteoarthritis who are overweight or obese.

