Given that people with OA who are overweight or obese tend to experience more severe symptoms [19, 20] and are more likely to undergo joint replacement surgery [21], weight loss is an important component of management. However, although weight loss is recommended by evidence-based guidelines [4, 22, 23] there is only limited evidence to support its efficacy in improving symptoms of pain and dysfunction. In the literature, interventions often combine both exercise and weight loss components, making it difficult to identify the independent effects of weight loss on outcomes. One pivotal trial involving 454 overweight and obese adults with knee OA investigated the effects of an intensive diet program, with and without exercise, conducted in a rigorously monitored environment [24]. The combined diet and exercise group lost approximately 10% of body weight, compared to 2% in the exercise only group, leading to reduced knee loads and inflammation compared to the exercise only group. While statistically significant benefits on pain (1-point difference (95% confidence interval: 0.3 to 1.7) on 20-point scale) and function (4.3-point difference (2.1 to 6.5) on 68-point scale) were also seen, the magnitude of these benefits are small and may be of questionable clinical importance. Furthermore, although the diet and exercise intervention was reported to be more cost-effective than usual care (pharmacological NSAIDs regimen followed by total knee replacement surgery) [25], the cost-effectiveness analyses did not include data from the exercise only group. Thus, it remains unknown whether a combined intervention of diet and exercise is more cost-effective than exercise alone.

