Economic evaluations will assess and compare the cost-effectiveness of the interventions. This will involve analysis of: i) cost per extra person with a clinically significant improvement in pain (measured as 1.8 point reduction on the pain score) and function (6 unadjusted WOMAC units), and; ii) per quality-adjusted life years (QALYs) gained for the intervention compared to control at 12 months. QALYs will be calculated based on utility scores using the AQoL-8D at baseline and 12 months. The difference in health care usage and productivity lost between baseline and 12 months will be compared for intervention and control groups. The association between utility gains on the AQoL-8D and productivity will also be compared between the intervention and control groups.

To evaluate the longer-term effects of the *Exercise* and *Exercise plus weight management* interventions on total knee joint replacement and knee arthroscopy surgical rates, logistic regression models for surgery will be fit using generalised estimating equations to account for clustering by physiotherapist and dietitian, with treatment effects summarised using risk differences and 95% confidence intervals. The stratifying variable of history of knee surgery will be adjusted for.

To evaluate whether there is a relationship between amount of weight loss and changes in pain and/or function, linear regression models for changes in pain and outcome will be fit and will include a term for weight lost at 6 and 12 months (as percentage of baseline weight), adjusting for baseline level of the outcome, assigned treatment group, and stratifying variables. Demographic variables thought to affect both weight loss and outcomes levels, including age and sex, will also be included in the model. Fractional polynomial terms for weight lost will be assessed to investigate if the relationship between outcomes and weight loss is non-linear. Standard diagnostic plots will be used to assess regression assumptions. We will also evaluate whether there is a relationship between adherence to exercise and changes in pain and/or function by estimating a complier-average causal effect using a two-stage least squares approach [76].

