## Discussion

With the rapidly rising burden of knee OA, there is an urgent need for interventions that improve outcomes and that are also widely accessible to people in rural, regional, and metropolitan communities [89]. Although the effectiveness of exercise therapy on pain and function is well-established, there is relatively limited robust evidence about the additional benefits of weight loss in people with knee OA [4].

This trial will be the first to investigate the clinical- and cost-effectiveness of a remotely delivered service combining dietary weight management and exercise, compared to a service involving exercise only and to an online information-only control group. Such a service has the potential to be a low-cost and accessible way in which people with OA can receive care, thus potentially increasing uptake of recommended management methods, like weight loss and exercise. Findings from this study will inform healthcare providers about the effects of incorporating weight loss components into exercise interventions. Moderator analyses using data from this study will also allow us to determine whether specific sub-groups of participants are more likely to respond to these remotely delivered services, which will allow health service providers to better target interventions to those that would benefit most. Qualitative explorations will provide insight into the feasibility and viability of implementing similar weight management programs into private and public healthcare settings from the perspective of both the participants receiving care, as well as the clinicians involved in delivering it.

A potential limitation of this trial is the targeted sample of participants, including only those who are Medibank Private members with a level of membership that includes arthroplasty surgery. This may potentially limit the generalisability of our findings, however, Medibank Private is one is one of the largest providers of private health insurance in Australia, and participants will be recruited Australia-wide to attempt to maximise the generalisability of the cohort.

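### The economic paragraph names only control as comparator for cost per QALY, health-care use and productivity, which does not match the stated aim of judging the cost-effectiveness of adding weight management to exercise

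*Protocol article*

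**What the plan says.** **The question.** The abstract's aim concerns the "clinical- and cost-effectiveness of a remotely-delivered, evidence- and theory-informed, behaviour change intervention targeting exercise and self-management", to be compared "with the same intervention plus active weight management" and with the information-only group. The Background section gives the evidence gap: "it remains unknown whether a combined intervention of diet and exercise is more cost-effective than exercise alone". The Discussion presents as new an assessment of "clinical- and cost-effectiveness of a remotely delivered service combining dietary weight management and exercise, compared to a service involving exercise only", with control as a further comparator. Under Trial sample size, the effect size of 0.3 between the two active arms is defended partly on cost-effectiveness, "given the considerable expense of the weight management program relative to the exercise components of this combined intervention".

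**The planned analysis.** The economic paragraph under Analysis begins: "Economic evaluations will assess and compare the cost-effectiveness of the interventions". It then lists two ratios. The first is the "cost per extra person with a clinically significant improvement in pain" and in function, with no comparator directly attached. The second is cost "per quality-adjusted life years (QALYs) gained for the intervention compared to control at 12 months". The next two sentences contrast intervention with control on health-care use and lost productivity, and on the association between utility gains and productivity.

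**The clinical contrasts.** The first paragraph under Analysis lists all three pairs of arms, including the two active arms against each other, but for primary and secondary outcomes and determinants. Table 4 places health economic data, QALYs and the cost-effectiveness ratio under its heading for other measures.

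**The concern.** The three arms are mutually exclusive options, and one of them is another option plus an expensive addition. The funder or any adopter faces two steps: is Exercise worth its cost over information alone, and is the weight programme worth its further cost over Exercise? The paragraph as written attaches a comparator to the first kind of step only. A ratio of the combined arm against control mixes the gain bought by the exercise component with the gain bought by the diet component. It can look acceptable when the added component, taken by itself, is not.

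The singular noun adds a second problem. There are two interventions, so the wording could mean each arm in turn, one particular arm, or both arms pooled. Pooling would remove the contrast that the Background identifies as unknown.

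This is more than detail left out of a condensed article. The article does state a comparator, and that comparator does not fit its own aim.

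**Working it through.** **Step 1: is there a figure to reproduce?** None for the economic evaluation. The article gives no costs, utilities or expected QALY differences. The point therefore rests on comparing the sections and on the algebra of the ratios.

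**Step 2: which contrast does each part name?**

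| Place in the article | Combined vs Exercise | Active arm vs control |
|---|---|---|
| Abstract, aim (cost-effectiveness) | yes | yes |
| Background, evidence gap | yes | no |
| Discussion, stated contribution | yes | yes |
| Analysis, clinical outcomes | yes | yes |
| Analysis, opening economic sentence | open (plural, no pairs named) | open |
| Analysis, cost per extra responder | no comparator attached | no comparator attached |
| Analysis, cost per QALY | not named | yes |
| Analysis, health-care use and productivity | not named | yes |

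The cost contrast that the aim calls for is not written out anywhere in the analysis text.

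**Step 3: how do the ratios relate?** Let C_E and Q_E be the mean extra cost and extra QALYs of Exercise over control, and C_W and Q_W the same for the combined arm.

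- Exercise vs control: R_E = C_E / Q_E
- Combined vs control: R_W = C_W / Q_W
- Combined vs Exercise: R_inc = (C_W − C_E) / (Q_W − Q_E)

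Since C_W = C_E + (C_W − C_E), dividing by Q_W gives

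R_W = (Q_E/Q_W) × R_E + (1 − Q_E/Q_W) × R_inc.

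When Q_W > Q_E > 0, the combined arm's ratio against control is thus a weighted average of the two steps. Whenever the second step is poorer value than the first, R_W lies below R_inc and flatters the added component.

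**Step 4: illustration.** All inputs are assumed, in arbitrary currency units: C_E = 600, Q_E = 0.030, C_W = 1,800. Then R_E = 600/0.030 = 20,000, and the extra cost of the second step is 1,800 − 600 = 1,200.

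| Assumed Q_W | R_W = 1,800/Q_W | R_inc = 1,200/(Q_W − 0.030) |
|---|---|---|
| 0.060 | 30,000 | 1,200/0.030 = 40,000 |
| 0.040 | 45,000 | 1,200/0.010 = 120,000 |
| 0.032 | 56,250 | 1,200/0.002 = 600,000 |
| 0.030 | 60,000 | no QALY gain for 1,200 more: dominated |

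Check of the identity in the second row: 0.75 × 20,000 + 0.25 × 120,000 = 15,000 + 30,000 = 45,000. In the last row the combined arm is dominated by Exercise, yet its ratio against control is still finite.

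**Step 5: can the incremental result be recovered?** From the two ratios alone, no: R_E and R_W do not fix R_inc without the QALY shares. From arm-level costs and QALYs, yes, by the subtraction in step 3. Its uncertainty cannot be read from two separate intervals against control, because both share the control arm; it has to be estimated directly from participant data.

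**The case against.** The other side has several sound points.

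- The opening economic sentence commits to comparing the interventions, in the plural, and the abstract's Methods say the cost-effectiveness of each will be assessed. The responder ratio has no comparator of its own, and whether the closing words about control reach back to it is unclear. A reader might infer that the plan confines every economic ratio to control. The text does not support that.
- A reader might also infer that the trial cannot answer the incremental question. That is wrong. Table 4 schedules medication use, service use, work productivity and the AQoL-8D at baseline, 6 and 12 months without restricting them to particular arms, so the incremental ratio can be computed.
- Much of the effect side is already specified. The AQoL-8D is a secondary outcome and so falls under all three pairwise comparisons, and the proportion reaching the minimal important difference on each primary outcome is compared across groups. What is missing is the cost side of the active-arm pair and the QALY contrast as such.
- The aim sentence that closes the Background section speaks of effectiveness only. The abstract, the evidence gap and the Discussion nevertheless include cost.
- Rules for dominated options, net benefit and acceptability curves are detail that an article may leave to a fuller plan, which is not shown. Their absence is no fault here.

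These points narrow the finding without removing it. A general promise to compare the interventions does not say which contrasts will be made, and every economic comparator that is named is control.

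**Conclusion.** The point holds as a mismatch between the stated economic question and the comparators written into the analysis. For cost per QALY, health-care use and productivity, control is the only comparator named, and the text does not say which of the two interventions is meant. Ratios against control do not by themselves show whether the weight programme justifies its cost over Exercise.

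The size in this trial is unknown. The weighted-average relation in the working is exact when both arms gain QALYs over control and the combined arm gains more. The numerical range is purely illustrative and depends on the assumed inputs; it does not predict what the trial will find. No figure in the article changes.

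This should be corrected before the economic data are analysed. Otherwise the contrast the trial was partly motivated by is left to be defined after results are seen.

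**What to change.** In the economic paragraph under Analysis, replace the generic reference to intervention and control with named arms, and state that the following will be estimated with their uncertainty:

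1. Exercise versus control, and Exercise plus weight management versus Exercise: incremental cost per QALY and incremental cost per extra responder on pain and on function.
2. The matching differences in health-care use and productivity for the same two contrasts.
3. Any ratio of Exercise plus weight management versus control, reported in addition to these and not in their place.

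The paragraph should also say that the two active arms are not pooled, or give the reason if they are. The method for expressing uncertainty and the handling of dominated options can go in the full economic plan.

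The cost is a few sentences and a little more analysis. No new data, participants or questionnaires are needed. One practical downside is that the QALY difference between the active arms may be small, making that ratio unstable, so its uncertainty should be shown alongside it.
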